## Abstract

**Introduction:**

Current treatments for Alzheimer's and other neurodegenerative diseases have only limited effectiveness meaning that there is an urgent need for new medications that could influence disease incidence and progression. We will investigate the potential of a selection of commonly prescribed drugs, as a more efficient and cost-effective method of identifying new drugs for the prevention or treatment of Alzheimer's disease, non-Alzheimer's disease dementias, Parkinson's disease and amyotrophic lateral sclerosis. Our research will focus on drugs used for the treatment of hypertension, hypercholesterolaemia and type 2 diabetes, all of which have previously been identified as potentially cerebroprotective and have variable levels of preclinical evidence that suggest they may have beneficial effects for various aspects of dementia pathology.

**Methods and analysis:**

We will conduct a hypothesis testing observational cohort study using data from the Clinical Practice Research Datalink (CPRD). Our analysis will consider four statistical methods, which have different approaches for modelling confounding. These are multivariable adjusted Cox regression; propensity matched regression; instrumental variable analysis and marginal structural models. We will also use an intention-to-treat analysis, whereby we will define all exposures based on the first prescription observed in the database so that the target parameter is comparable to that estimated by a randomised controlled trial.

**Ethics and dissemination:**

This protocol has been approved by the CPRD's Independent Scientific Advisory Committee (ISAC). We will publish the results of the study as open-access peer-reviewed publications and disseminate findings through national and international conferences as are appropriate.

Strengths and limitations of this studyThis study will involve a large sample of data and has considerable power to detect even relatively small effects, even under highly conservative Bonferroni corrections. For example, the sample to assess the progression of dementia contains 105 471 patients and has a minimum detectable HR of 0.931.We plan to use four different statistical methods in our analysis, which have different approaches for modelling confounding. By doing this, we will be able to assess the merits of each method in the given situation in order to minimise confounding.Dementia is a heterogeneous outcome, and electronic codes used to define cases in primary care may not be as accurate as cases in clinical cohorts. We will undertake sensitivity analyses to explore how this may affect our results.

## Introduction

### Rationale

Alzheimer's disease (AD) is a progressive disease affecting brain function and independent living and eventually requires full-time care. There are only a few treatments that temporarily help symptoms such as memory loss; however, these eventually become ineffective as the underlying disease progresses unabated. Part of the difficulty of treating AD is that it involves the activation of many destructive processes in the brain, each of which is likely to need simultaneous treatment if the progression of the disease is to be halted.

For this reason, there is urgent need for new evidence about medications that could influence the incidence and progression of AD. One promising approach is to investigate drug repositioning,^1^ which offers a time-effective and cost-effective alternative to traditional drug development. A recent consensus study of dementia experts identified a short-list of individual and classes of prescribed drugs that may be repurposed as novel treatments for dementia.^2^ The short-list included compounds used to treat hypertension, hypercholesterolaemia and type 2 diabetes, all of which can be classed as having ‘cerebroprotective’ properties and have variable levels of preclinical evidence that suggest they may have beneficial effects for various aspects of dementia pathology. However as yet there is limited pharmacoepidemiological data to support their effects in human populations. Therefore, we plan to investigate whether these existing medications could be repurposed to prevent or treat AD.

Furthermore, the overlap of different forms of neurodegenerative disease would suggest that there may be scope to translate existing or newly identified interventions for testing in neurodegenerative diseases where similarities exist. Thus, we will start by examining the most common form of neurodegenerative disease—AD.^3^
^4^ We will then investigate whether the drug candidates could also be repurposed to treat or prevent other neurodegenerative diseases—these will include other non-Alzheimer's disease dementias (NADD) (ie, the group for dementias in which AD is not thought to play a part), Parkinson's disease (PD) and amyotrophic lateral sclerosis (ALS). Collectively, these findings will allow the prioritisation of drugs to be tested as repurposed treatments in clinical trials of AD and other neurodegenerative diseases in the future.

### Objectives

To investigate whether commonly prescribed medications, previously identified as potentially cerebroprotective, are associated with the incidence or progression of neurodegenerative disease.

We will focus on the following medications:
Treatments for hypertension.Treatments for hypercholesterolaemia.Treatments for type 2 diabetes.

Along with the following neurodegenerative diseases:
Alzheimer's disease (AD).Non-Alzheimer's disease dementias (NADD).Parkinson's disease (PD).Amyotrophic lateral sclerosis (ALS).

## Methods and analysis

### Study design

We will conduct a hypothesis testing observational cohort study of neurodegenerative disease incidence and progression, using data from the Clinical Practice Research Datalink (CPRD).

### Participants

We will include men and women older than 40 years, with at least 12 consecutive months of records classified as ‘acceptable’ by the CPRD from all ‘up to standard’ practices.^5^ Patients registered at a practice <365 days before their 40th birthday, or those with a first record of one of the index drug classes of interest before their 40th birthday will be excluded. This will ensure high-quality assessment of baseline data and possible confounders.

### Sample selection

We will investigate the incidence and progression of AD, NADD, PD and ALS. Our investigations into the incidence will focus on treatments which are reported to be cerebroprotective and are currently prescribed for hypertension,^6^ hypercholesterolaemia^7^
^8^ and type 2 diabetes.^9^ For each treatment, we will conduct two analyses. The first will compare treated to untreated individuals with similar indications—this is cohort A. The second will compare the outcomes of individuals given different subclasses of specific medications—this is cohort B. We will also investigate progression using a third cohort, cohort C. Progression will be defined as the postdiagnosis survival of a patient. For each neurodegenerative disease group of interest, we will determine the effects on progression of the three possible new treatments. In cohort C, exposure will be defined in two ways: (1) using patients being prescribed these drugs at the time of diagnosis of their neurodegenerative disease; and (2) using those issued new prescriptions postdiagnosis. The structure of these three cohorts is summarised in table 1 and further explained in the text that follows. All of the cohorts rely on defined diagnoses and exposures, which are recorded in the CPRD through the use of Read and product codes, respectively. Read codes uniquely identify clinical terms recorded by the general practitioner (GP) during a consultation, while product codes uniquely identify prescriptions issued. Both types of code are recorded with a date, and this will be used to determine the dates of diagnosis and exposure required to define the cohorts.

**Table 1 BMJOPEN2016012044TB1:** Comparison of the three cohort types

	Cohort A	Cohort B	Cohort C
Purpose	To investigate incidence by comparing treated and untreated individuals.	To investigate incidence by comparing the different drug subclasses of each treatment.	To investigate progression by comparing treated and untreated individuals.
Number of cohorts required	There will be three cohorts of this type, one for each treatment of interest.	There will be three cohorts of this type, one for each treatment of interest.	There will be three cohorts of this type, one for each of dementia (AD or NADD), PD and ALS.
Exposures	Treatments for hypertension, hypercholesterolaemia and type 2 diabetes.	Treatments for hypertension, hypercholesterolaemia and type 2 diabetes.	Treatments for hypertension, hypercholesterolaemia, and type 2 diabetes.
Start of follow-up (index date)	Date at first risk of the condition the treatment is used for or date of first diagnosis of the condition itself if there was no preceding period ‘at risk’.	Date of first prescription of a treatment of interest.	Date of first diagnosis of neurodegenerative disease of interest.
Outcome	Diagnosis of neurodegenerative disease of interest.	Diagnosis of neurodegenerative disease of interest.	Death.
Exclusion criteria	Individuals with <12 consecutive months of records prior to cohort entry.	Individuals prescribed treatment and control medications at the same time or with <12 consecutive months of records prior to cohort entry.	Individuals with <12 consecutive months of records prior to cohort entry.
Statistical analysis	Conventional regression, propensity score regression, instrumental variable analysis and marginal structural models.	Conventional regression, propensity score regression, instrumental variable analysis and marginal structural models.	Conventional regression, propensity score regression and marginal structural models.

AD, Alzheimer's disease; ALS, amyotrophic lateral sclerosis; NADD, Non-Alzheimer's disease dementias; PD, Parkinson's disease.

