#### Cohort C

For each neurodegenerative disease group of interest, we will create a cohort of individuals with a read code indicating this outcome (see online supplementary file 4) or a product code indicating they received treatment for the outcome (see online supplementary file 5). These cohorts will be used to investigate the associations of neurodegenerative disease progression with exposure to one of the three treatment groups of interest: treatments for hypertension, treatments for hypercholesterolaemia and treatments for type 2 diabetes. We will investigate both exposure before and after the diagnosis of a neurodegenerative disease. For all of the treatments we consider, each cohort will be split into ‘exposed’ and ‘unexposed’ groups. In the analysis, individuals in the ‘exposed’ group, that is, those who were prescribed the treatment under investigation, will be compared with individuals in the ‘unexposed’ groups, that is, those who did not receive the treatment.

10.1136/bmjopen-2016-012044.supp4supplementary file

10.1136/bmjopen-2016-012044.supp5supplementary file

Follow-up for cohort C will start with the first recorded read code indicating AD or other neurodegenerative disease (see online supplementary file 4) or, in the absence of a diagnosis, the first recorded product code indicating they received treatment for a neurodegenerative disease (see online supplementary file 5). Follow-up will end with the earliest of death or censoring due to the end of registration at a CPRD general practice.

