### Data sources

The main data source for this project is the CPRD. Cause-specific mortality from linked ONS data is more accurate than CPRD data on mortality from general practices.^13^ Therefore, we will use the ONS data to identify date and cause of death and test our hypotheses relating to mortality using data from linked practices only. We will also be using the Index of Multiple Deprivation (IMD) in order to define socioeconomic position, which is listed as a covariate in our analysis.

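### Cohort C labels death from any cause as progression while testing vascular and metabolic drugs, and no stated analysis uses the cause of death it obtains

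*Protocol article*

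**What the plan says.** The objective is to find out whether the drugs "are associated with the incidence or progression of neurodegenerative disease". Cohort C carries the progression half. Sample selection gives the definition: "Progression will be defined as the postdiagnosis survival of a patient". Table 1 states the purpose of cohort C as "To investigate progression by comparing treated and untreated individuals". In its outcome row, the cohort C cell holds the single word for death, next to the diagnosis outcome of cohorts A and B. The Cohort C section closes follow-up on the same terms: "Follow-up will end with the earliest of death or censoring due to the end of registration at a CPRD general practice". The exposures there are "treatments for hypertension, treatments for hypercholesterolaemia and treatments for type 2 diabetes".

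On cause of death, Data sources says "we will use the ONS data to identify date and cause of death" and gives the greater accuracy of ONS cause-specific mortality as the reason for the linkage. The Outcomes section takes deaths from ONS without restricting by cause.

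The naming of the estimate varies. The section on multivariable Cox regression speaks of survival, whereas the section on marginal structural models speaks of progression.

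**The concern.** The article never prints the phrase all-cause, but unqualified death combined with follow-up that ends at any death amounts to it. The drugs under test are prescribed for vascular and metabolic conditions, so they have a route to longer survival that need not pass through the brain disease. An HR below 1 therefore fits two explanations, slower neurodegeneration or fewer vascular and metabolic deaths, and the plan's label names only the first.

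None of the stated methods separates the two. Adjusting for coronary and cerebrovascular history, propensity matching and marginal structural models all address who receives the drug. They do not remove the drug's own later effect on vascular death, which is part of the effect being estimated. Table 1 does not list instrumental variables for cohort C. The Bias and Confounding sections do not mention the issue. At stake is what cohort C may be said to show when, as the Rationale puts it, "these findings will allow the prioritisation of drugs to be tested as repurposed treatments in clinical trials of AD and other neurodegenerative diseases".

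**Working it through.** **Inputs from the article (Table 3, Study size).** Minimum detectable HRs in cohort C: dementia 0.931 (N = 105 471), PD 0.870 (N = 20 686), ALS 0.600 (N = 2227), at α = 0.05. The printed β of 0.80 is read as power 0.80, and a two-sided test is assumed. Each HR refers to the smallest exposed group.

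**Can 0.931 be reproduced?** Not fully. The exposed share p and the number of deaths D are not in the article. Inverting Schoenfeld's formula:

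D·p(1 − p) = (1.960 + 0.842)² / (ln 0.931)² = 1535.5

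With all 105 471 patients dying, this implies an exposed share of 1.5%; with half dying, 3.0%; with 30% dying, 5.1%. The figure is attainable but cannot be confirmed. The point does not depend on it.

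**Size of the ambiguity.** Let s be the vascular share of deaths in the unexposed, r the drug's HR for vascular death, and let the drug have no effect on any other death. Then

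all-cause HR ≈ (1 − s) + s·r = 1 − s(1 − r).

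The article gives neither s nor r, so all values below are assumptions.

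| s | r = 0.85 | r = 0.80 | r = 0.75 | r = 0.70 | r needed for 0.931 = 1 − 0.069/s |
|---|---|---|---|---|---|
| 0.10 | 0.985 | 0.980 | 0.975 | 0.970 | 0.31 |
| 0.20 | 0.970 | 0.960 | 0.950 | 0.940 | 0.66 |
| 0.30 | 0.955 | 0.940 | 0.925 | 0.910 | 0.77 |
| 0.40 | 0.940 | 0.920 | 0.900 | 0.880 | 0.83 |

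**Dementia.** Part of the grid lies beyond 0.931 (for example s = 0.30, r = 0.75) and part does not (s = 0.20 at every r shown). The 0.931 is the 80%-power point, not the edge of significance. The implied standard error of ln HR is 1/√1535.5 = 0.0255, so significance begins near exp(−1.96 × 0.0255) = 0.951. In the smallest exposed group, power to declare an all-cause HR of 0.96, 0.94 or 0.92 is 36%, 68% or 90%.

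**PD and ALS.** For s from 0.20 to 0.40 and r from 0.70 to 0.85, the lowest value is 1 − 0.40 × 0.30 = 0.880. That does not reach 0.870 or 0.600. At s = 0.40, PD would need r = 1 − 0.130/0.40 = 0.675, and ALS would need r = 1 − 0.400/0.40 = 0, that is, every vascular death prevented. Larger exposed groups would detect smaller effects than Table 3 shows, but their sizes are in supplementary files that are not shown.

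**The case against.** The strongest reply is that the definition is open. The reader is told that progression means survival after diagnosis, so a reader who holds to that definition is not misled, and survival is a practical proxy in primary-care records. This stands in part: the all-cause result is worth reporting. It does not justify the name, since the stated definition turns any survival gain into a progression effect.

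Four stronger readings are tempting, and the documents do not support them.

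- *Cause of death is never going to be used.* Data sources stresses the accuracy of cause-specific mortality, which suggests that its use was contemplated, and the full protocol is not shown. The supportable statement is that no analysis stated in this article uses it.
- *A drug will be prioritised on a false cohort C result.* The Rationale prioritises on the findings taken together, and cohorts A and B measure diagnosis, not death. No section prioritises on cohort C alone.
- *An HR above 1 belongs to the same fault.* An excess of deaths that reflects the illness behind the prescription is confounding by indication. The Confounding section names it and the Covariates section adjusts for vascular history and the Charlson Index. That adjustment may be partial, but it is a separate matter.
- *The artefact clears the detectable HR throughout cohort C.* It does so only for dementia, and only under some assumed values.

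It is also fair to say that residual confounding could push the net estimate the other way. That makes the direction of error less predictable; it does not turn all-cause death into a measure of progression.

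**Conclusion.** The point holds as one of endpoint definition and labelling. Cohort C's only outcome is all-cause death, it is called progression, and the drugs tested can alter it through vascular or metabolic deaths alone. The article states no analysis that would tell the two apart, although the data for one are being obtained.

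The size is not known. In dementia, an effect confined to vascular deaths could pass the detectable HR of 0.931 if vascular deaths are about 30% or more of the total and the drug's vascular HR is about 0.77 or lower. With a 20% share it would need about 0.66, and with 10% about 0.31, so the artefact would then be small. For PD and ALS the detectable HRs are not reached in the range examined. These results assume no effect on non-vascular deaths.

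A reader might infer that cohort C can contribute nothing to the progression objective. That goes too far: it gives a valid question about survival, and cause-specific results would narrow the interpretation.

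**What to change.** 1. In Sample selection, Table 1, the Cohort C section and the section on marginal structural models, name the outcome 'post-diagnosis survival (all-cause)' and keep it as a reported result.
2. Add two cause-specific Cox analyses in cohort C from the ONS data, censoring deaths from other causes at death: (a) the neurodegenerative disease as underlying cause; (b) a cardiovascular or diabetic underlying cause. In the dementia cohort, count vascular dementia codes under (a). Otherwise disease-related deaths could be lost from the non-Alzheimer's group, if its code list (not shown) includes vascular dementia.
3. State in advance that an all-cause effect will not be interpreted as slower progression when it appears in (b) but not in (a). Say how 'appears' will be judged from the reported HRs and confidence intervals.
4. State as a limitation that even (a) is a mortality proxy for progression.

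The cost is two further outcomes on data already being obtained, in the linked practices already used for mortality, so no patients are lost. The downside is fewer events per outcome, hence wider intervals, above all in ALS, and some misclassification of certified cause.

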### Bias

There are three main sources of bias in our results: ascertainment bias, collider bias and immortal time bias. To overcome ascertainment bias, we will control for consultation rate in our analyses because people who have more chronic conditions such as hypertension, diabetes or renal insufficiency may have higher rates of consultation, which may also increase the opportunity for recording other diagnoses such as dementia. Collider bias could occur if we conditioned on events that happened as a result of the prescription the patient was issued. To prevent this form of bias from affecting our results, we will define each covariate using data inputted prior to the index date.^14^ Finally, we will minimise the risk of immortal time bias in two ways. First, to prevent misclassified immortal time, we will define exposures based on the first prescription observed in the database^10^ and use an intention-to-treat analysis. Second, to minimise immortal time, we will follow-up patients (exposed and unexposed) from a consistent index date. This will be a test result or a read code indicating diagnosis where possible;^15^ however, to capture all relevant patients, we will allow those receiving treatment without a recorded diagnosis to be included.

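### Cohort C reads survival from recorded diagnosis as progression without allowing for lead time: patients already treated at diagnosis may be recorded earlier, and the three methods share that start date

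*Protocol article*

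**What the plan says.** **Outcome and clock.** Sample selection: "Progression will be defined as the postdiagnosis survival of a patient". Table 1 gives the cohort C index date as "Date of first diagnosis of neurodegenerative disease of interest". The Cohort C section agrees: "Follow-up for cohort C will start with the first recorded read code indicating AD or other neurodegenerative disease", with a treatment code used where there is no diagnosis code. Follow-up ends at death or end of registration.

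**Exposure.** There are two definitions. The first is formed "using patients being prescribed these drugs at the time of diagnosis of their neurodegenerative disease"; the second, "using those issued new prescriptions postdiagnosis". Each exposed group is compared with patients who did not receive the treatment.

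**Bias.** The Bias section says: "There are three main sources of bias in our results: ascertainment bias, collider bias and immortal time bias". Under ascertainment bias it notes that people with chronic conditions such as hypertension or diabetes "may have higher rates of consultation, which may also increase the opportunity for recording other diagnoses such as dementia", and answers that "we will control for consultation rate in our analyses".

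**Covariates and methods.** The Covariates section lists lifestyle, deprivation, vascular history, the Charlson Index and consultation rate, but nothing on the stage of the neurodegenerative disease at diagnosis. It forms consultation rate from visits before the index date, divided by the length of follow-up. Table 1 gives cohort C Cox regression, propensity score regression and marginal structural models, without the instrumental variable analysis.

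**The concern.** In cohort C everyone has the disease recorded, so extra contact with the practice can no longer change whether it is recorded. It can still change when. The conditions the Bias section gives as reasons for more contact include two that the study drugs treat. Patients on those drugs at diagnosis may therefore start follow-up earlier in the disease, and the interval gained is counted as survival even if the drug does nothing.

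The article relies on comparing methods to expose uncontrolled confounding. That cannot work here, because the three cohort C methods share one start date. The Introduction says the results will help prioritise drugs for clinical trials, and the sample is large enough for a small artefact to be statistically significant. As planned, earlier recording and slower progression could not be told apart.

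**Working it through.** **1. The plan's own figure.** Table 3 gives 105 471 dementia patients and a minimum detectable HR of 0.931, with α = 0.05 and 0.80 (printed as β, read here as power; two-sided assumed). By Schoenfeld's formula, D·p·(1−p) = (1.960 + 0.842)² / (ln 0.931)² = 7.849 / 0.005112 ≈ 1535.5, where D is deaths and p the exposed share. That is 6142 deaths at 1:1. The implied smallest exposed share is 1.5% if all patients die, 3.0% if half die and 5.1% if 30% die. The figure is plausible, but the article gives neither D nor p, so it cannot be reproduced. It serves below as a yardstick.

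**2. Apparent HR when the true HR is 1.** The documents give no lead time, survival after diagnosis or hazard shape, so all of these are assumed. Two mechanisms were simulated, with a Cox model from recorded diagnosis.

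- *Fixed death dates:* exposed survival = the same random draw + L. Set (i): exponential or Weibull shape 1.3, mean survival 3-6 years, 30% exposed, uniform censoring over 0-12 years. Set (ii): exponential, median 3-6 years, 1:1, censoring at 10 years.
- *Shared disease clock:* Weibull mortality from onset, mean onset-to-diagnosis 2 years, exposed diagnosed L earlier, everyone alive at their own diagnosis included. Either median survival 3-6 years, 1:1 and censoring at 10 years, or mean survival from onset 5 or 8 years, 30% exposed and uniform 0-12 year censoring.

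| Model | L = 3 months | 6 months | 12 months | L giving 0.931 |
|---|---|---|---|---|
| Fixed death dates, set (i) | 0.90-0.93 | 0.80-0.86 | 0.65-0.75 | about 2-3 months |
| Fixed death dates, set (ii) | 0.94-0.96 | 0.88-0.92 | 0.78-0.85 | about 3.5-5 months |
| Shared clock, shape 2.0 | 0.94-0.96 | 0.88-0.92 | 0.77-0.84 | about 3.5-5 months |
| Shared clock, shape 1.5 | 0.97-0.98 | 0.93-0.95 | 0.87-0.90 | about 6-8 months |
| Shared clock, shape 1.3 | 0.97-0.99 | 0.96-0.97 | 0.90-0.92 | about 9-10 months |
| Shared clock, shape 1.0 | 1.00 | 1.00 | 1.00 | never |

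The last column is linear interpolation. For example, shape 1.5 with median 4 years gives 0.943 at 6 months and 0.888 at 12, so 6 + 6 × 0.012/0.055 = 7.3 months.

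**3. Does consultation-rate adjustment remove it?** Shared clock, shape 1.5, median 4 years, 60 000 patients (Monte Carlo error about 0.01):

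| Source of lead | Mean lead | Unadjusted HR | Adjusted HR |
|---|---|---|---|
| Through the rate only | 2.9 months | 0.967 | 1.00 |
| Rate plus another route | 5.9 months | 0.933 | 0.954 |
| Rate plus a larger other route | 8.9 months | 0.907 | 0.932 |

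A correctly measured rate removes the lead that passes through it and no more. If the denominator is read literally as post-index follow-up, the covariate contains the outcome, and adjusting for it on the log scale gave HRs of 0.58-0.61 with no drug effect.

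**4. Does delaying the exposed start work?** Delaying it by the true lead, and dropping exposed patients who die or leave before then, returned HRs of about 1.00-1.01. With no lead at all the same step over-corrects. At shape 1.3 with hazard rising from diagnosis it gave 1.04-1.05 at a 2-month delay, 1.09-1.12 at 6 months and 1.16-1.22 at 12. With hazard running from onset at the same shape, a 12-month delay gave 1.06-1.08.

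**The case against.** **The size depends on the model.** Fixing death dates means no exposed patient can die in the first L months. When everyone alive at their own diagnosis can enter, the bias is smaller, and under constant hazard it vanishes. This stands. A reader might infer that two or three months of lead would by itself yield 0.931; only the fixed-death-date model with set (i) gives that.

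**The direction is not established.** A reader might infer that the bias must favour the drug. The Bias section says only that such patients may consult more. The Cohort A and Confounding sections warn that an unexposed group drawn from the full population is likely to be healthier, and cohort C requires no indication in its unexposed group. With an assumed comorbid mortality ratio of 1.2, the apparent HR stayed above 1 even at 12 months of lead (1.03 or more) for shapes up to 1.5; at shape 2.0 it fell below 1. The objection stands as to net direction. Two opposing biases of unknown size still do not make the result interpretable as progression.

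**The plan already acts on the mechanism.** It adjusts for consultation rate, and step 3 shows that this can suffice if all the lead passes through the rate. So it would be wrong to say that the plan ignores the problem. Whether other routes exist is an assumption. The Bias section's rule that covariates use pre-index data also suggests that pre-index time is the intended denominator.

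**The scope is limited.** New prescriptions after diagnosis are less exposed to lead from earlier treatment, and the protocol's example is dementia, not PD or ALS.

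**Conclusion.** The concern holds in a limited form. For patients already on treatment at diagnosis, a survival difference in cohort C cannot be separated from earlier recording, and comparing the three methods will not help. Consultation-rate adjustment removes only the part of the lead that acts through a correctly measured rate.

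With a true HR of 1, 0.931 is reached at roughly 2-3 months of lead if only the clock moves (3.5-5 months under the second set of inputs). It takes about 4-10 months if mortality rises with disease duration, and is never reached under constant hazard. These figures rest on assumed survival, censoring, onset-to-diagnosis delay and hazard shape. They show what a lead of months could do, not that such a lead exists. The documents do not support saying that treated patients are in fact diagnosed earlier, that the net bias favours the drug, or that every cohort C contrast is affected alike.

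**What to change.** 1. Name lead time as a possible bias for the first exposure definition of cohort C.
2. Define consultation rate as pre-index visits divided by pre-index record time, in line with the Bias section's own rule for covariates.
3. Pre-specify a sensitivity analysis that delays the exposed group's start of follow-up over a range, for example 2, 3, 6 and 12 months, excluding exposed patients who die or leave before the new start. Report the lead at which the HR reaches 1. State that the analysis can over-correct if there is no lead, so it is read as a range and not as a corrected estimate.
4. Adjust for markers of disease stage at diagnosis only where they are recorded.
5. Describe the outcome as survival after recorded diagnosis, and qualify any reading as slower progression by the result of step 3.

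The cost is protocol wording and one repeated set of cohort C models on data already held. The drawback is more cautious conclusions for some contrasts.
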